### **8.2 Statistical analysis**

Three populations will be defined:

- Intention to treat (ITT) population: the set of all randomized participants.
- Per-protocol (PP) population: the set of all randomized participants, excluding cases with protocol violation, or withdrawal on patients willing.
- Safety analysis population: the set of all randomized participants.

Baseline variables will be presented as median with 25th-75th percentile or frequencies with percentages. The primary endpoint will be analyzed using the Chi-Squared Test. The secondary endpoints and safety outcomes will be compared by the Chi-Squared Test, Fisher's exact test, or Wilcoxon rank-sum test, as appropriate.

Results will be presented as relative risk (RR) with 95% confidence intervals (CIs). All statistical analyses will be performed using SPSS software (v26.0; SPSS Inc., Chicago, IL, USA), with significance set at a two-sided  $\alpha$  level of 5%.

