| Study design                 | Multi-center, open-label, randomized, controlled trial                                                                                                                                                                                                                                                                                                                                                                                                                                                                                                                                                                                                       |
| Primary objective            | To compare the efficacy and safety of Low-molecular-weight heparin (LMWH) plus insulin versus insulin alone in reducing the incidence of new-onset organ failure and/or mortality among patients with hypertriglyceridemia-associated acute pancreatitis (HTG-AP).                                                                                                                                                                                                                                                                                                                                                                                           |
| Study center(s)              | Up to 10 study centers                                                                                                                                                                                                                                                                                                                                                                                                                                                                                                                                                                                                                                       |

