## **4 STUDY PROCEDURES**

### **4.1 Randomization and masking**

Patients will be randomly assigned (1:1) to either LMWH plus insulin (LMWH + insulin group) or insulin alone (insulin group). Dynamic randomization will be used via a network-based center random software (Churun Information Technology Co, Ltd, Guangzhou, China). The randomization and masked allocation assignments will be conducted by the sub-investigator from each entity.

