## **8 STATISTICAL CONSIDERATIONS**

### **8.1 Sample size**

This study is designed as a superiority trial, and the sample size is calculated based on data from previous clinical studies. The occurrence rate of the new-onset organ failure and/or mortality of LMWH combined with insulin in HTGP patients is 8.3%, whereas that for treatment with insulin alone in HTGP patients is 17.86%. We estimate that a sample size of 490 participants will provide 80% power at a two-sided alpha level of 0.05 to detect a 9.56% reduction in the composite primary endpoint. Given an attrition rate of 10%, we plan to randomize 540 patients in total (270 per group). The sample size was calculated using PASS software (PASS V.11, NCSS software, Kaysville, USA).

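### The primary endpoint is tied to an unadjusted chi-squared test although allocation is dynamic; adjusting the relative risk would be a cheap and modest gain

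*Protocol*

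**What the plan says.** Protocol section 8.2 names one test for the primary composite of new-onset organ failure and death: "The primary endpoint will be analyzed using the Chi-Squared Test". On the effect measure it says "Results will be presented as relative risk (RR) with 95% confidence intervals (CIs"). It mentions no covariate, stratification factor or centre term.

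Section 4.1 sets a 1:1 ratio and then says "Dynamic randomization will be used via a network-based center random software". Neither that section nor the synopsis says which factors the dynamic scheme balances. The synopsis gives the size of the network as "Up to 10 study centers".

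Section 8.1 plans for 8.3% on LMWH plus insulin against 17.86% on insulin alone. It asks for 490 evaluable patients (540 randomised) for 80% power at two-sided 5% "to detect a 9.56% reduction in the composite primary endpoint".

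On entry data, section 3.3 makes age, triglyceride and time from onset eligibility criteria, so all three are known before randomisation. The Introduction links higher triglyceride to persistent SIRS and organ failure. Figure 2 schedules baseline variables but does not list them.

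**The concern.** Dynamic randomisation steers each assignment so that the arms stay alike on chosen factors. Where those factors predict outcome, the between-arm difference varies less than under simple randomisation. The ordinary chi-squared test still uses the simple-randomisation variance. Its p-value is then somewhat too large and the matching interval somewhat too wide. An analysis that includes the balancing factors restores the right width. Adding a few prognostic entry variables can gain a little more.

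This is not detail left for the analysis plan. The protocol states the primary test, and an analysis plan that adjusted it would depart from the protocol. What is at stake is some precision and power. A positive result from the unadjusted test would still be valid.

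**Working it through.** **1. The plan's own figure.** Inputs from section 8.1: p1 = 0.083, p2 = 0.1786, d = 0.0956, mean p = 0.1308, two-sided 5%, 80% power.

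n per group = [1.960·√(2·0.1308·0.8692) + 0.8416·√(0.083·0.917 + 0.1786·0.8214)]² / 0.0956² = [1.960·0.4768 + 0.8416·0.4720]² / 0.00914 = 194.1, so 195 per group or 390 in total.

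Other two-sided versions give 430 (continuity-corrected), 384 (unpooled) and 380 (arcsine). The stated 490 is not reproduced at 80% power. The closest version found is 486, at 85% power with continuity correction. The stated number is therefore generous.

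**2. Power of the unadjusted test.** Power = Φ[(0.0956·√n − 1.960·0.4768)/0.4720].

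- n = 245 per group (490): Φ(1.190) = 88.3%
- n = 270 per group (540): Φ(1.348) = 91.1%

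Expected events at 490: 245 × 0.1786 + 245 × 0.083 = 43.8 + 20.3, about 64.

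**3. Size and power under balanced allocation.** Simulation with 10 centres and 6,000 trials per cell. Permuted pairs within strata stand in for a tight dynamic scheme. Strata are centre, or centre by a split of one covariate where a covariate is present. The comparison is unadjusted chi-squared against a logistic score test adjusted for centre (and the covariate). Marginal rates are the protocol's. The SDs, on the logit scale, are assumptions. N = 540:

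| Centre SD / covariate SD | Size, unadjusted | Size, adjusted | Power, unadjusted → adjusted |
|---|---|---|---|
| 0 / none | 5.1% | 5.2% | 91.6 → 92.0% |
| 0.3 / none | 4.7% | 5.0% | 91.3 → 91.8% |
| 0.5 / none | 4.6% | 5.1% | 91.2 → 92.0% |
| 0.8 / none | 4.4% | 5.3% | 91.2 → 92.3% |
| 0.3 / 0.5 | 4.9% | 5.9% | 91.5 → 92.4% |
| 0.5 / 1.0 | 4.3% | 5.7% | 92.1 → 94.1% |

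The Monte Carlo standard error of a size is √(0.05·0.95/6000) = 0.3 points, so the milder rows are hard to tell from 5%. At N = 490, centre SDs of 0.3 and 0.5 gave unadjusted sizes of 4.8% and 5.1%. The adjusted score test ran at or slightly above 5%, so part of the power gain is not real.

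**4. What this means for the interval.** If the standard error used is k times the true one, size = 2Φ(−1.960k). A size of 4.9% gives k = 1.969/1.960 = 1.004. A size of 4.3% gives k = 2.024/1.960 = 1.03. The interval is then about 0.4 to 3% too wide.

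**5. Upper end.** Suppose allocation balanced the whole risk score, with SD 0.7 / 1.0 / 1.4 at N = 490. Unadjusted size falls to about 4.0 / 3.4 / 2.4% (6,000 trials; a second run of 20,000 gave 4.1 / 3.8 / 2.6%). Power at the protocol's rates goes from 88 to 90%, 90 to 92% and 90 to 94%. Now balance only centre (SD 0.3) and a split of one of four covariates with the same total SDs. Size is then 4.5 / 4.5 / 4.3%, and a modified Poisson model gains about 0, 2 and 4 points.

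**6. Smaller true effect.** For illustration, take 12.13% on LMWH plus insulin, an assumed rate that is not in the protocol. The formula in step 2 gives about 43% unadjusted power at 490. With the whole risk score balanced, adjustment moved simulated power from 42 to 46%, 42 to 47% and 43 to 52% for the three SDs.

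**The case against.** The case against is substantial, and most of it limits the size of the point.

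- A reader might infer that allocation is balanced across centres and that the test is therefore conservative. The documents do not support this. The description of the software mentions a centre, but no balancing factor is stated. With non-prognostic factors the level holds (5.1% simulated).
- A reader might infer that power is wasted. On the protocol's own rates the unadjusted test has 88 to 91% power against a target of 80%. Powers below 50% need a smaller effect than the one planned.
- A size of 2.4 to 4.1% requires a scheme that balances all prognostic information. An unspecified dynamic scheme cannot be credited with that.
- A reader might assume that a baseline modified Marshall score is on file, because the endpoint excludes failure before randomisation. The protocol uses that score to define the outcome and does not list it as a baseline item.
- Chance imbalance in a factor outside the scheme is already covered by the test's type I error, so it does not make the test invalid.
- A long model is risky. Nine centre terms plus four covariates make 13 parameters, and 64/13 is about five events each.
- Covariate lists are commonly left to the analysis plan, which is not shown.

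All of this stands except the last point as a full answer. The missing list is no fault in itself, but section 8.2 positively fixes an unadjusted primary test.

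**Conclusion.** The point holds as a modest improvement to a stated rule. It is not an error that threatens validity. If the balancing factors are prognostic, the unadjusted test runs at about 4.3 to 4.9% under moderate assumptions, and its interval is up to about 3% too wide. Size falls further only with very strong balanced predictors. If the factors are not prognostic, nothing is lost.

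At 17.86% v 8.3%, adjustment adds roughly 0.5 to 2 points to power that already exceeds the target, and about 4 points with very strong predictors. The absolute gain can be larger if the true effect is smaller than planned. The departure is in the safe direction. Every predictor strength used here is an assumption, because the protocol gives none.

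**What to change.** Name the dynamic-randomisation factors. Reword section 8.2 so that the primary analysis is a relative risk with 95% CI adjusted for:

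- those factors, with centre (if it is one) pooled for small sites or fitted as a random effect;
- a short prespecified list of entry variables already measured for eligibility: log triglyceride, age and hours from onset;
- a baseline organ-function score, only if it is recorded.

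Modified Poisson regression with robust variance, or standardised logistic regression, gives the effect measure that section 8.2 already asks for. Keep the chi-squared test as supportive.

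The cost is a wording change, slightly more analysis work and a few degrees of freedom. With about 64 expected events the list must stay short. No new data are needed for the three eligibility variables.

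Separately, the stated 490 should be reconciled with its inputs, which need about 380 to 430 at 80% power.

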## 1 INTRODUCTION

Acute pancreatitis (AP) is a common gastrointestinal disease with multiple causes, including gallstones, alcohol, and hypertriglyceridemia (HTG). Basolateral secreted or leaked pancreatic lipase-mediated triglyceride (TG) lipolysis may play an important role in the initiation and exacerbation of hypertriglyceridemia-associated acute pancreatitis (HTG-AP). This lipolysis process leads to the accumulation of free fatty acids (FFAs), which can cause cytotoxic injury to the pancreas. Notably, increased serum TG levels have been linked to worse clinical outcomes, manifesting as persistent systemic inflammatory response syndrome (SIRS) and organ failure.

On that basis, there have been some treatment strategies introduced to reduce serum TG levels, including noninvasive measures such as fasting, insulin, and heparin, as well as invasive blood purification techniques. Despite these interventions, international guidelines for the early management of AP did not give any recommendations regarding specific TG-lowering therapy due to the lack of solid evidence. Nonetheless, in some clinical settings, insulin with or without heparin has emerged as a common therapeutic approach for the early management of HTG-AP. Heparin, including low-molecular-weight heparin (LMWH), stimulates the release of endothelial lipoprotein lipase (LPL) into circulation, while insulin activates LPL and reduces the activity of hormone-sensitive lipase, thereby increasing the clearance of chylomicrons from plasma.

Although heparin with insulin is commonly used for lowering-TG in the treatment of HTG-AP, the efficacy and safety of LMWH plus insulin in HTG-AP remains controversial. Our previous RCT showed that LMWH plus insulin not only rapidly decreased the TG levels within 48 hours, but also significantly decreased the incidence of respiratory failure in HTG-AP patients. Additionally, heparin might reduce pancreatic necrosis and improve organ function, by its anti-inflammation and antioxidative properties. However, the bleeding risk of low-molecular-weight heparin (LMWH) was significantly lower than that of unfractionated heparin, and it exerts

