### **3.3 Inclusion criteria**

- Patients aged between 18 and 85 years;
- AP diagnosed according to the 2012 revised Atlanta Classification;
- Time from AP onset to randomisation within 48 hours;
- Serum TG levels ranged from 11.3 mmol/L (equal to 1000 mg/dL) to 40 mmol/L (equal to 3550 mg/dL);

- Signed informed consent.

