### 5.2 Secondary endpoints

All the endpoints are assessed and collected within one month after randomization including 1) New-onset organ failure including respiratory failure, renal failure, and circulatory failure; 2) Mortality; 3) The time to achieve the TG goal of <5.65 mmol/L, which will be detected using a fully automated blood biochemistry analyzer; 4) New-onset SIRS; 5) Necrotizing pancreatitis; 6) Infected pancreatic necrosis; 7) Sepsis;

8) Pulmonary infection; 9) Vein thrombosis; 10 ) Pseudoaneurysm; 11) Sinistral portal hypertension; 12) Abdominal compartment syndrome; 13) Cerebral hemorrhage; 14) Demand for mechanical ventilation; 15) Renal replacement therapy; 16) Percutaneous drainage of ascites; 17) Drainage of pancreatic necrosis; 18) Debridement of pancreatic necrosis; 19) Vascular interventional therapy; 20) Duration of intensive care unit stay; 21) Length of hospital stay; 22) Hospital costs.

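### Time to the triglyceride goal is compared with an unadjusted test although entry triglyceride, known for every patient, sets the distance to the goal: valid, but precision is given up

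*Protocol*

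**What the plan says.** Protocol section 5.2 lists 22 secondary endpoints. The third is "The time to achieve the TG goal of <5.65 mmol/L, which will be detected using a fully automated blood biochemistry analyzer".

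Section 3.3 makes entry TG a condition of eligibility: "Serum TG levels ranged from 11.3 mmol/L (equal to 1000 mg/dL) to 40 mmol/L (equal to 3550 mg/dL"). Every eligible patient therefore has a TG value before randomisation.

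Section 8.2 gives one sentence for all secondary and safety outcomes: "The secondary endpoints and safety outcomes will be compared by the Chi-Squared Test, Fisher's exact test, or Wilcoxon rank-sum test, as appropriate". For a time, the test on that list that fits is the rank-sum test. The protocol names no adjusted or stratified analysis for any endpoint.

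Section 4.1 says "Dynamic randomization will be used via a network-based center random software" and lists no balancing factors. Section 1 gives TG clearance as part of the rationale: heparin "stimulates the release of endothelial lipoprotein lipase (LPL) into circulation".

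**The concern.** The endpoint measures how long a patient takes to get from an individual starting value to a common threshold. The starting value is thus built into the endpoint. A patient who enters at 11.3 mmol/L needs TG to halve once, while one who enters at 40 mmol/L needs it to halve almost three times. At equal clearance rates the second patient takes much longer, whichever arm they are in.

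A rank-sum test treats that difference as noise. A true difference in clearance between the arms is then harder to see than it need be, on an endpoint that bears directly on the TG-lowering rationale. The value that would remove part of the noise has already been collected. At stake is the precision of one secondary comparison. The primary endpoint is not affected.

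**Working it through.** **Figure in the plan.** There is none to reproduce. The protocol states no effect size, standard deviation or power for this endpoint, and section 8.1 concerns only the composite primary endpoint. The 80% below is a reference point, not a planned power for this comparison.

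**Step 1: distance to the goal.** The inputs are the entry limits of 11.3 and 40 mmol/L (section 3.3) and the goal of 5.65 mmol/L (section 5.2).
- Lower limit: ln(11.3/5.65) = 0.69, an absolute fall of 5.65 mmol/L.
- Upper limit: ln(40/5.65) = 1.96, an absolute fall of 34.35 mmol/L.
- Ratio: 1.957/0.693 = 2.8 on the log scale and 34.35/5.65 = 6.1 on the absolute scale.

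These are the extremes that eligibility allows. The spread among enrolled patients may be narrower.

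**Step 2: gain from adjustment.** Let r be the correlation of entry TG with time to goal within arm. Adjusting multiplies the variance of the treatment comparison by 1 − r². If unadjusted power is 80% at two-sided 0.05, adjusted power is Φ[(1.960 + 0.842)/√(1 − r²) − 1.960]. The protocol gives no r, so a range is shown. The last column is 540/(1 − r²).

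| r (assumed) | 1 − r² | Adjusted power | 540 patients carry the information of |
|---|---|---|---|
| 0.2 | 0.96 | 81.6% | 562 |
| 0.3 | 0.91 | 83.6% | 593 |
| 0.4 | 0.84 | 86.4% | 643 |
| 0.5 | 0.75 | 89.9% | 720 |
| 0.6 | 0.64 | 93.8% | 844 |

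**Step 3: which r is plausible.** A simulation used 270 per arm, entry TG log-uniform or right-skewed on 11.3 to 40, exponential TG decline with a median rate of 0.6 per day, and daily readings to Day 5, with later times tied at Day 6. It compared the rank-sum test with a regression of the ranked times on arm and ranked entry TG. All rates and effects are assumptions. The treatment effect was chosen separately for each SD to put unadjusted power at about 80% or higher.

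| Between-patient SD of log rate | Shift in log rate | Rank correlation | Unadjusted power | Adjusted power |
|---|---|---|---|---|
| 0.3 | 0.13 | 0.57 to 0.64 | 91 to 94% | 99% |
| 0.5 | 0.16 | 0.42 to 0.47 | 83 to 86% | 92% |
| 0.8 | 0.22 | 0.28 to 0.32 | 82% | 86% |
| 1.2 | 0.32 | 0.19 to 0.22 | 80% | 80 to 82% |

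The correlation, and with it the gain, falls as clearance rates become more variable.

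**Step 4: same effect, different variability.** A second simulation used 486 patients (540 less 10%), a median rate of 0.5 per day and the same reading schedule.
- At SD 0.5 to 0.7 with clearance 9 to 20% faster, adjustment gained about 4 to 10 points of power.
- At SD 1.0, or where unadjusted power was already near its ceiling, it gained about 1 to 3 points.
- Type I error of the adjusted analysis was about 4 to 5%, and adjustment never lowered power.

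**The case against.** The strongest reply is that nothing here is invalid. Randomised arms can be compared by a rank-sum test without baseline adjustment, and many trials do so for secondary endpoints. This stands. A reader might infer that a chance imbalance in entry TG would bias or invalidate the result, more so because section 4.1 names no balancing factors. The protocol does not support that. The error rate of the unadjusted test already allows for chance imbalance, and whether the dynamic scheme balances entry TG is simply not stated.

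A second reply is that covariate adjustment is matter for a statistical analysis plan, and that the closing words of the section 8.2 sentence leave room for it. This is partly fair. But the sentence names a list of three tests, none of which can adjust, so the point concerns what the protocol fixes rather than what it omits.

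A third reply concerns size, and it stands. A reader might infer a large gain from a favourable scenario. With SD 0.3 and a shift of 0.28 SD, power rises from 54% to 79%. That scenario assumes very uniform clearance and a treatment that speeds it by only about 9% (exp(0.28 × 0.3) = 1.088). With the same SD and 20% faster clearance, power is 99% without adjustment. No input in the protocol favours the first scenario.

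A reader might also take this endpoint as the only efficacy test of mechanism. Section 1 also cites anti-inflammatory and antioxidative effects, on which endpoints such as new-onset SIRS bear.

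Last, a time-to-goal regression cannot be specified without a rule for patients who die or never reach the goal. This is correct, and the fix has to state one.

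**Conclusion.** The point holds as one of efficiency on a single secondary endpoint. The named test is valid but discards a baseline value that is known for every patient and sets the distance to the goal.

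The direction is secure: it follows from a fixed threshold and a wide entry range. The size is not given by the protocol. If unadjusted power were 80%, adjustment would bring it to between about 82% (r = 0.2) and 94% (r = 0.6). Values of r towards the lower end go with widely varying clearance rates, and there the gain is slight. The simulated figures rest on assumed exponential decline, assumed rates and effects, and daily readings to Day 5. The claim does not extend to bias, to an inflated error rate, or to the primary analysis.

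**What to change.** In section 8.2, name the main comparison for time to TG below 5.65 mmol/L as a rank-based analysis of covariance: ranked times regressed on arm and log entry TG, taking the last value before randomisation as a continuous covariate. State that patients who do not reach the goal are ranked as the longest times.

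A time-to-goal regression with the same two terms is an acceptable alternative once the protocol states how non-reachers and deaths are handled. It would also give an effect estimate with an interval. Keep the unadjusted rank-sum test as supportive.

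The change needs no new data, visits or patients. It costs one more model term, a stated rule for non-reachers, and a result slightly less simple to present than a difference in medians. Fixing it in advance also avoids a choice about adjustment after the results are seen.

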### **4.3 Intervention Group (LMWH + insulin group)**

In the LMWH + insulin group, a 4000 IU of LMWH sodium injection (enoxaparin) will be injected subcutaneously once every 12 hours for three days. Continuous usage of LMWH at prophylactic dosages will be considered for patients assessed to be at high-highest risk of venous thromboembolism and low bleeding risk, which was on chief physician's discretion.

For those with a glucose level > 11.1 mmol/L, patients will receive micropumps of insulin at 2 to 6 U/h, monitor blood glucose closely, to maintain the serum glucose levels between 7.8 and 10 mmol/L. When the glucose levels fall below 7.8 mmol/L, 6 U of insulin will be added to 500 mL of 5% glucose for intravenous infusion until the TG levels decrease to less than 5.65 mmol/L (500 mg/dL) or for a maximum duration of 5 days after randomization, whichever occurs first. For those with a glucose level ≤11.1 mmol/L, patients will receive 6 U of insulin with 500 mL of 5% glucose for intravenous, twice a day for 5 days, if hypoglycemia occurs, 5% dextrose change to 10% dextrose.

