## 5 OUTCOMES

### 5.1 Primary endpoint

The primary endpoint is a composite of new-onset organ failure and mortality within one month after randomization, excluding events occurring within 24 hours before randomization. Organ failure includes respiratory failure, renal failure, and circulatory failure, which is defined as a score of 2 or more using the modified Marshall scoring system^28.

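### Time to the triglyceride goal is a time-to-event endpoint, but the plan's list of tests has no method for censoring, no rule for patients who never reach the goal or die, and RR as its only effect measure

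*Protocol*

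**What the plan says.** Protocol section 8.2 covers all secondary and safety outcomes in one sentence: "The secondary endpoints and safety outcomes will be compared by the Chi-Squared Test, Fisher's exact test, or Wilcoxon rank-sum test, as appropriate". The effect measure follows: "Results will be presented as relative risk (RR) with 95% confidence intervals (CIs"). No other effect measure and no time-to-event method is named.

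Section 5.2 lists 22 secondary endpoints. Number 3 is "The time to achieve the TG goal of <5.65 mmol/L". The last three are "20) Duration of intensive care unit stay; 21) Length of hospital stay; 22) Hospital costs". On the window it says "All the endpoints are assessed and collected within one month after randomization".

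The protocol foresees patients without an observed time to goal:

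- Section 4.3 continues one insulin regimen until the goal or "for a maximum duration of 5 days after randomization, whichever occurs first". Section 4.5 likewise stops insulin at the goal or at 5 days, and section 4.6 provides for patients whose TG is still raised at that point.
- Section 5.1 makes death part of the main outcome: "The primary endpoint is a composite of new-onset organ failure and mortality within one month after randomization".
- Section 8.1 allows for 10% attrition.

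No sentence says what value such patients receive.

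**The concern.** The words 'as appropriate' choose among three tests; they do not add a fourth. Chi-squared and Fisher's exact tests are for categories, so by elimination the rank-sum test is left for a time. That test needs a rank for every patient. A patient who withdraws or is discharged on Day 2 above the goal has a time known only to exceed 2 days, and the ordinary test has no place for that information.

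Patients followed to a common cut-off without reaching the goal can be ranked, but only under a rule, and none is written. In an open-label trial (section 4.2), a rule chosen after the data are seen is open to challenge. If non-achievers are simply left out, the comparison conditions on the outcome: the slower arm loses more of its slow patients, and the arms look more alike than they are. The endpoint matters because the introduction rests the rationale largely on TG lowering.

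Relative risk has no natural meaning for a time, a number of days or a cost. A related, smaller question is how deaths enter ICU and hospital stay: if raw days are ranked, an early death takes one of the shortest, apparently favourable, ranks.

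**Working it through.** The protocol gives no figure for this endpoint, so there is none to reproduce. Section 8.1 is used only for the number of patients: 490 / 2 = 245 per arm.

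**Assumptions (not in the protocol).** Exponential times to goal; TG measured daily, so times are rounded up to whole days; common cut-off at the end of Day 5; no withdrawals. The proportion p not at goal by Day 5 is varied.

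**Rates.** λ = −ln(p) / 5 per day; median = ln 2 / λ.

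- p = 0.25 (control): λ = 1.386 / 5 = 0.277, median 2.5 days.
- p = 0.15 (LMWH): λ = 1.897 / 5 = 0.379, median 1.8 days.

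**Effect of dropping non-achievers on the medians.** Among achievers the median is −ln(1 − 0.5(1 − p)) / λ.

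- Control: −ln(0.625) / 0.277 = 1.70 days.
- LMWH: −ln(0.575) / 0.379 = 1.46 days.

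On this continuous scale a true difference of about 0.67 days shrinks to about 0.24. On the day-rounded scale the true medians are 3 versus 2, and the achievers' medians are about 2 versus 2.

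**Simulated power, two-sided 5%, 245 per arm.** Repeated runs of 1,500 to 4,000 replicates agree to within about 2 points in the first two rows and 3 points in the third.

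| Not at goal by Day 5, control vs LMWH | Log-rank, all patients | Rank-sum, achievers only | Rank-sum, all patients, non-achievers tied worst |
|---|---|---|---|
| 25% vs 15% | about 86% | about 26% | about 81% |
| 40% vs 25% | about 97% | about 21% | about 95% |
| 10% vs 5% | about 78% | about 40% | about 71% |

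**Cross-check with other inputs.** With 270 per group, control median 3 days and cut-off at Day 5, rate ratios of 1.3 and 1.5 give 16% and 33% for achievers only, and 69% and 97% with a tied worst rank. With no effect the rejection rates are 4.6% and 5.5%, so here the issue is power and a distorted estimate, not type I error.

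**ICU and hospital stay.** The protocol gives no rate for mortality alone; section 8.1 gives only the composite, which "is 8.3%, whereas that for treatment with insulin alone in HTGP patients is 17.86"%. Assume 270 per group, identical stay in survivors (lognormal, median 10 days, log-scale SD 0.5) and deaths between Days 1 and 4. A rank-sum test on raw days then rejects at these rates:

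| Mortality by arm | Rejections |
|---|---|
| 2% vs 2% | 4.8% |
| 1% vs 3% | 5.8% |
| 2% vs 5% | 9.6% |
| 2% vs 10% | 36% |

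The distortion leans toward the arm with more deaths. It is close to nominal when the mortality difference is small.

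**The case against.** The strongest reply is that section 8.2 is a short summary that assigns no test to any endpoint, and that rules for non-achievers, deaths and continuous effect measures are ordinary content of a statistical analysis plan, which may exist but is not shown. This stands for the handling of deaths in the stay endpoints, where the protocol is only silent. It stands less well for the TG endpoint: there the protocol does not leave the method open but names three tests, none of which accommodates censoring. A later plan could name a time-to-event method only by going beyond that list.

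Three stronger readings are tempting, and the documents do not support them.

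- *The rank-sum test cannot handle non-achievers.* It can. It needs ranks, not exact times, and with a common cut-off and complete follow-up a tied worst rank costs only about 2 to 7 points of power against log-rank in the scenarios above. What it does not accommodate is loss before the cut-off.
- *The trial will drop non-achievers.* No sentence says so, and it would sit badly with an intention-to-treat set of all randomised participants. The large power loss comes from exclusion, not from the test.
- *The plan scores early deaths as good outcomes.* This follows only if raw days are ranked, which the protocol neither states nor rules out.

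The 5-day limit also caps insulin, not the endpoint, whose window is one month. It shows that non-achievement by Day 5 is foreseen, but gives no rate.

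**Conclusion.** The concern holds in limited form. The listed tests and the single effect measure do not fit an endpoint that the protocol itself defines as a time to an event, and no rule covers patients who miss the goal, die or leave.

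The cost ranges from small to severe according to an unstated choice. Under the assumed non-achievement rates, power is about 21% to 40% if non-achievers are dropped, about 71% to 95% with a tied worst rank, and about 78% to 97% with log-rank. All of this rests on assumed exponential times, daily measurement, a Day 5 cut-off and no withdrawals.

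The stay endpoints warrant only a secondary recommendation: the bias depends on mortality rates that the protocol does not give. Every affected endpoint is secondary, and the primary analysis is untouched. The change should be made, but the trial's main conclusion does not hang on it.

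**What to change.** In section 8.2:

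1. Analyse time to TG below 5.65 mmol/L from randomisation as time-to-event in all randomised patients, censored at the last TG measurement, with death as a competing event. Report cumulative incidence curves, a log-rank or Gray test, and a hazard ratio with 95% CI.
2. At minimum, keep the rank-sum test but apply it to all randomised patients, with a stated cut-off and a tied worst rank for non-achievers and deaths, and say how withdrawal or discharge before the cut-off is treated.
3. Restrict RR to binary outcomes. For times, days and costs give a suitable measure, for example a Hodges-Lehmann difference with CI.
4. As a secondary recommendation, state that deaths are scored worst in ICU and hospital stay, or add days alive and out of ICU or hospital to Day 28. The latter is a different quantity from length of stay and should be labelled as such.

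The cost is wording, settled before the data are examined. Figure 2 already schedules secondary endpoints on Days 1 to 5 and Day 28. Since it shows no assessments in between, the cut-off should be chosen with that gap in mind.
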